### Ethics

The study was reviewed and approved by the University of Plymouth Faculty Research Ethics and Integrity Committee and Health Research Authority on 24/08/2023 and 07/09/2023 respectively (reference 23/HRA/3635).

The data arising from the study will be owned by the Sponsor. On completion of the study, the data will be analysed and tabulated, and a Final Report prepared. This report will be submitted to the Sponsor and Funder (Baily Thomas Charitable Fund) and will be accessed on request by contacting PenCTU. Participating investigators will not have rights to publish any of the study data without the permission of the CI and Sponsor.

## Results

The results section in this paper will outline the practical challenges that have been encountered when setting up the study.

### Trial status

At the time of submission, the current approved protocol version is V1.0 16.08.2023. The first site received green light authorisation on 30.11.2023 and patient identification commenced thereafter. The data collection end date is 01.04.2024.

### Administrative and technical

In the initial stages of the study, discussions were held surrounding whether patients prescribed Clozapine should be excluded from data collection. It was confirmed that these patients should be excluded, and the reasons for this are described in the methods and analysis section. As this was confirmed prior to the study's submission to the HRA, this was included in the protocol and therefore was made clear to sites in the protocol and during the site initiation visits. Once the study received HRA approval and sites started to open, it was queried whether patients who had been prescribed Promethazine Hydrochloride for agitation were eligible. It was noted that whilst the medication is not often prescribed for that indication, it is nevertheless an antipsychotic and when prescribed for agitation, patients could be included in the study. This was then fed back to the participating site.

As the study is a cross-sectional study that occurs over 7 annual time-points, the 1st July was identified as the census date for each yearly timepoint. This meant that sites have been asked to select the information and clinic letter that that occurred as close to this date as possible, though noting that data can be extracted from any point between 1st Jan–31st Dec for each timepoint. Originally, the 1st January was selected as the census date, but discussion within the trial management group found that this date may not have been the most efficient due to it being around Christmas and New Year. The census date of 1st July was selected as the mid-point of that year, so that data could be extracted from anywhere from 1st January–31st December, so long as the patient had had a psychiatric review in that year timepoint of interest.

Administrative and technical practical challenges such as those described above are bound to occur during the study's progress, and often participating sites may have queries that are perhaps not clarified into the study protocol. As the study is a feasibility study, practical challenges allow the study team to learn from them and take them into consideration when developing the protocol for a future definitive study.

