First generation APTs (most common brand name)^c^	Chlorpromazine (Largactil)—Levomepromazine (Nozinan)—Pericyazine (Neulactil)—Prochlorperazine (Stemetil)—Promazine—Trifluoperazine (Stelazine)—Benperidol (Frenactyl)—Haloperidol (Haldol)—Flupenthixol (Depixol; Fluanxol)—Zuclopenthixol (Clopixol)—Pimozide (ORAP)—Sulpiride		x
Second generation APTs (most common brand name)^c^	Amisulpride (Solian—oral route)—Aripiprazole (Abilify)—Asenapine—Cariprazine—Lurasidone—Olanzapine—Paliperidone—Quetiapine—Risperidone		x
Other^c^	Pipothiazine—Penfluoridol—Fluphenazine—Thioridazine—Other (free text)		x
Reason for each APT prescribed	Psychotic disorder		x
	To manage specific behavioural challenges/agitation		x
	To augment other psychotropic medication		x
	Anxiety disorder		x
	Other		x
	Not clearly indicated		x

^a^
Time-point: Most recent clinic letter to the 1st of July of the year under study; 6 months either side (e.g., 01/06/2017: between 1st January 2017 and 31st December 2017).

^b^
Co-occurring medical conditions, based on those most commonly reported in patients with ID.

^c^
Dose, units, frequency, and route of administration are recorded for each APT prescribed.

Data will be extracted from multiple sources for each patient by the clinical team. Source data will come from paper-based clinic letters, inhouse databases (e.g., clinical portal bespoke)/electronic systems (e.g., SystmOne, Rio, Care Notes). The yearly census date is the 1st of July and the patient's most recent information, and clinic letter will be identified (up to 6 months before or 6 months after the census date). Collected data will be anonymised at site by the clinical team and/or research nurses.

Data will be entered directly onto a study specific instance of REDCap (Research Electronic Data Capture), a secure web-based database. De-identified data will also be transferred on the SPC tool to evaluate and track the prescription changes over time. Only anonymised (de-identified) data will be available to the University of Plymouth research team/data processors for analysis. As the data is de-identified at site before being entered into the database, each year will be treated as independent even if patients are eligible year on year. There will be no patient linkage across time.

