### Dose equivalent methods

To account for the different treatment doses of APT, data will be aggregated into a standardized form. Each patient's oral and long-acting IM injectable APT regime will be represented by their chlorpromazine equivalent dose values (14, 25), which offers a means of standardization for APT (14).

Chlorpromazine is a commonly used APT and a CPZ-equivalent dose is defined as a dose of antipsychotic that is comparable to 100 mg of CPZ. This is commonly used in clinical and research settings. It provides a universal language of APT burden that is readily understandable for healthcare professionals, researchers, policy makers, and the lay public alike.

There is no accepted standard for equivalence calculation and many methods have been documented with associated strengths and limitations. The study will utilise the Defined Daily Dose (DDD) equivalence method, highlighted in Leucht's 2016 paper, ‘Dose equivalents for antipsychotic drugs: The DDD method’ (25). This study acknowledges the limitations of all dose equivalence methods as highlighted by Patel et al. (26) including minimum effective dose, dose response curve, DDD and various consensus methods. The Leucht's DDD method, including equivalence tables, has been selected as a consistent approach to calculating equivalence. It always provides a method for comparing antipsychotic equivalence between first- and second-generation APTs. The authors highlight that this study is not intended to test equivalence methods, only to apply a consistent approach to calculation.

To facilitate conversion of APT to chlorpromazine equivalent dose values, a pre-programmed script in R/Stata will be utilised, following relevant conversion formulas [as per that included in the supplementary table that accompanies the Leucht et al. (25) article].

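### A ruling that promethazine for agitation counts as an antipsychotic came after sites began to open, is reported as given to one site and is in neither protocol V1.0 nor Table 1, so sites may apply the two-drug threshold differently

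*Protocol article*

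**What the plan says.** Inclusion criterion 4 (Patient eligibility criteria and identification) requires two or more antipsychotics, oral or depot. It attaches no condition on indication and does not point to a drug list.

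Table 1 (Outcome measures) names the drugs to be recorded in three groups: first generation, second generation and Other. The first-generation row includes the run "Prochlorperazine (Stemetil)—Promazine—Trifluoperazine (Stelazine". Promethazine is named in none of the three groups, but the Other group ends with a free-text entry. Dose, units, frequency and route are recorded for every drug, and so is the reason for prescribing each one.

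Administrative and technical describes two drug decisions. The clozapine exclusion was settled before submission to the HRA and "was made clear to sites in the protocol and during the site initiation visits". The promethazine question, which concerned eligibility, came later: "Once the study received HRA approval and sites started to open, it was queried whether patients who had been prescribed Promethazine Hydrochloride for agitation". The ruling was that "it is nevertheless an antipsychotic and when prescribed for agitation, patients could be included in the study", and the article adds: "This was then fed back to the participating site". Trial status states that at submission of the article "the current approved protocol version is V1.0 16.08.2023".

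For the outcome, Dose equivalent methods says that "a pre-programmed script in R/Stata will be utilised, following relevant conversion formulas", taken from the supplementary table of the cited article on the DDD method.

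**The concern.** Both the study population and its main outcome depend on which drugs count as antipsychotics. The two-drug threshold decides who is recorded, and the summed chlorpromazine equivalent is what is compared. A person on one drug named in Table 1 plus promethazine for agitation is eligible under the ruling. A site that works from protocol V1.0 and the Table 1 names has nothing that tells it so.

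The study's stated purpose is to compare services, through summaries by site, a model with site as a random effect and the SPC tool. If services screen under different rules, part of any difference between them could reflect the rule and not the prescribing. Sites also contribute few records each year, so a single record is a visible share of a site-year.

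**Working it through.** The plan states no figure that rests on this point, so the check is mainly a comparison of the sections.

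1. **Timing.** Protocol V1.0 is dated 16.08.2023. The first site received green light on 30.11.2023. The query is placed after HRA approval, as sites were opening. V1.0 therefore predates the ruling, and no later version was in force when the article was submitted.
2. **Drug list.** Table 1 names promazine but not promethazine. The free-text entry means that a site can record promethazine. It does not tell a site that the drug counts towards the threshold, which has to be known earlier, when patients are identified from the caseload.
3. **Form of the rule.** Criterion 4 counts drugs whatever the reason for prescribing. The ruling counts promethazine when it is given for agitation. No drug named in Table 1 carries such a condition.
4. **Communication.** For clozapine, the article reports that all sites were told, in the protocol and at initiation visits. For promethazine, it reports feedback to one site and says nothing of the others.
5. **Dose.** A free-text entry needs its own conversion rule in a pre-programmed script. The article gives none for promethazine, and the cited conversion table is not shown. If the table has a factor, the total can be calculated and only the eligibility question remains. If it has none, the record is either not calculable (Objective 3) or its total omits that drug, and the article does not say which.
6. **Scale.** Input: 7 to 10 records per site per year (Target sample size and justification).
   - One affected record in a site-year: 1/10 = 10.0% to 1/7 = 14.3%.
   - One affected record in a site's seven-year total of 7 × 7 = 49 to 7 × 10 = 70 records: 1/70 = 1.4% to 1/49 = 2.0%.
   - The article records a person anew in each eligible year. One person eligible throughout would give 7/70 = 10.0% to 7/49 = 14.3% of the site's total.
7. **Effect on a site mean.** If k of n records have a mean total r times that of the remaining records, the site mean moves by (k/n) × (r − 1) relative to those remaining records. Neither k nor r is given, so no figure for the shift can be derived.

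**The case against.** The strongest reply is that the article never says sites behaved differently. It reports that a query was answered. A condensed article that does not mention a wider circular is weak evidence that none was sent, and other sites may already have counted promethazine. This stands. A reader might infer that eligibility and total dose do differ between sites, but the documents support only that they may.

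Second, the drug list is open. Criterion 4 is not limited to the names in Table 1, and free text is available, so the ruling clarifies an open category and does not contradict a closed one. This also stands, but it does not settle the matter, because an open category is where sites need the same instruction.

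Third, a reader might infer that promethazine has no convertible dose, and that the site mean and the calculable share under Objective 3 must therefore fall. That depends on a table that is not shown. It also needs a count of affected records, and the article itself says the drug is seldom given for this indication. No such fall can be claimed.

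Fourth, with site as a random effect, a constant offset at one site would largely be absorbed and would disturb the year trend little. This is fair for the trend. It does not protect the comparison between sites or the SPC charts.

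Finally, the authors disclose the episode openly as a lesson for a later study, and finding such ambiguities is part of a feasibility study. That is to their credit, but the present comparison of services still needs one rule.

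**Conclusion.** The point holds as a risk of inconsistency, not as a demonstrated difference. A rule that depends on indication, made after sites began to open, decides whether some people meet the two-drug threshold. It lies outside protocol V1.0, the drug is not named in Table 1, and it is reported as given to one site. Its reach depends on a number of records that is not given; the only firm scale is 10.0% to 14.3% of a site-year for each such record. The concern about dose holds only if the conversion table has no entry for the drug.

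This goes beyond a detail that could be left to an analysis plan, because it concerns who was identified at each site. The conclusion takes the article's account of the communication at face value and takes no view on how promethazine should be classified.

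**What to change.** Reconcile inclusion criterion 4, Table 1 and the ruling under Administrative and technical. State one rule for all sites, and say whether the other sites received it and when.

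For the main analysis, use records with two or more drugs from a list fixed in advance, each with a conversion factor in the chosen table. Identify records that reach two only through promethazine from the drug and reason fields already collected, reading the free-text entries by hand. Report their number by site and year, and include them in a sensitivity analysis. State in advance how their total is formed, and how they count under Objective 3, if the table has no factor for the drug.

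The cost is one added analysis and the loss of a few records from the main set; no new data field is needed. One limit remains. People on one listed drug plus promethazine who were never identified at sites unaware of the ruling left no record, so the sensitivity analysis cannot recover them. Data collection was due to end on 01.04.2024, so finding them would mean screening caseloads again. The sensitivity analysis should be reported with that caveat.

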### Identification

Another practical challenge that has occurred during the set-up of the study relates to the differing processes in discharging patients under each ID service. If an ID service is more likely to discharge a patient from their service sooner, it may result in having less eligible patients for the study. However, if the same patient remains under the ID service year on year, then there is the potential that the patient will be eligible to be recorded for each of the yearly timepoints and will therefore contribute to the site's identification target multiple times. This can then therefore lead to a difference in the number of eligible patients identified at each site. Though this is something that the study team do not have control over, it perhaps could be considered when confirming the recruitment targets for each study site.

### Research implementation

Implementing the outcome measures into the study protocol was another practical challenge that occurred during the study set-up. It is important that the outcome measures accurately reflect the study's objectives, and therefore a method had to be selected that allowed the APTs to be converted into equivalent doses so that the main objectives of the study could be tested. Chlorpromazine equivalent dose values were selected as they are commonly used in clinical and research settings, and therefore readily understandable for healthcare professionals, researchers and policy makers. Similarly, there is no accepted standard for equivalence calculation, and therefore Leucht's DDD (25) equivalence method was selected as it provides a method for comparing first- and second-generation APTs, which ensures that a consistent approach is applied to the calculation.

### Dissemination

The study will be reported in a manuscript that will be submitted to a peer-reviewed medical journal as open access. The group will also present results at relevant national and international conferences relevant to the mental health needs of adults with intellectual disability, such as the Royal College of Psychiatrist's Faculty of Intellectual Disability annual conference. Findings will also be presented to relevant ID organisations, including the Learning Disability National Professional Senate, The Challenging Behaviour Foundation, Speakup Self Advocacy, and Mencap. In addition to presenting the findings, reports will be provided in both standard and easy-read formats. Following the presentation, attendees will be asked to complete a brief semi-structured questionnaire to provide detailed feedback. This will help identify the views and priorities of the various stakeholder groups and help inform additional analyses to be incorporated into the final analysis and corresponding report.

## Discussion

There is a clear rationale for developing a database that establishes the antipsychotic prescribing patterns across specialist adult ID services, so that trends and patterns can be identified and further evaluated to improve the healthcare of PwID. Previous data has reported on prevalence prescribing rates, rather converting the APTs into dose equivalent values which can be input into the SPC tool to evaluate and measure ID specialist use of APTs in PwID across the UK. Furthermore, previous research has tended to report on entire clinical populations of PwID, rather than specifically a focus on those in receipt ≥2 different forms of APTs. This, along with the fact that there is currently no clinical rationale or evidence to support ≥2 different APTs being prescribed, supports the idea that there a need for a database to address this issue. However, the development of a de-identified database can present a series of unique benefits and challenges.

The limitations of the study are inherent to the use of routine health data. The use of routinely collected data means that the data quality and data completeness between sites might be vastly different. Site teams are encouraged to extract data from multiple sources, including clinic letters, inhouse databases and electronic or paper note systems. However, some of the data being collected might not be evident in any of these places and could potentially be difficult to find. This was acknowledged as a potential difficulty during study development and one of the feasibility objectives of the study is to evaluate whether it is indeed feasible to obtain a complete (or near complete) data set for each patient. An additional limitation of the study is that some patients may be in receipt of one or more of their APTs on a short-term basis.

The use of routinely collected data can result in a reduced burden for staff at participating NHS sites. Staff are not required to conduct any questionnaires with participants for this study and are advised to only use what is already available. Due to the fact the data is routinely collected and is de-identified at site level before being entered into the database, site staff are not required to receive consent from patients before their data is included, which again reduces the workload associated with the study which can be beneficial in sites where capacity is limited. Similarly, the non-requirement for consent procedures can also have great advantages in research with PwID who may be difficult to enrol in studies that require consent. It can also ensure that certain hard-to-reach patient groups are not missed, such as those who are unable to consent for themselves and do not have anyone who is able to provide advice on their behalf, which can lead to a lack of representation of this patient group in the study results.

This feasibility study is intended to inform decisions about the design of a wider registry that would involve antipsychotic prescribing data for patients across multiple sites nationwide. Once the prescribing patterns of those prescribed ≥2 APTs are further understood, it may allow for the opportunity to progress to obtain further understanding of the patterns across the country for those on one APT. By using the SPC tool as a validated means of plotting data, it can be utilised to see if it is possible to track yearly APT prescribing among PwID receiving multiple forms of APTs and monitor variation between services and patient groups (e.g., co-occurring mental health conditions, challenging behaviour) or not. This could allow researchers to identify trends and patterns of variation. If the use of the SPC tool proves successful, then the data collected across multiple participating trusts across the UK could be inputted into the SPC tool and used to evaluate and measure ID specialist service use of APTs in PwID nationwide.

## Data Availability

The original contributions presented in the study are included in the article, further inquiries can be directed to the corresponding author.
